**Methods:**

The study is designed as a 12-month randomized controlled trial with three parallel arms: (1) Web-based education, (2) Web-based education + mobile app (diet and exercise plan), (3) Usual care. The total study duration is 12 months with data collection at baseline, 3, 6, 9 and 12 months. We will enroll 408 Mexican adults with T2D, randomized equally across arms. Measurements at baseline, 3, 6, 9, and 12 months include A1c (primary outcome), lipid profile, anthropometry, body composition, quality of life, lifestyle, and physical activity.

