## Methods/design

### Objectives

The primary objective of this clinical trial is to assess changes in A1c when comparing web-only, web + app, and usual care.

The secondary objectives are to evaluate the effect of the intervention on:
Lipid profile [total cholesterol, LDL-c [low-density lipoprotein cholesterol], HDL-c [high-density lipoprotein cholesterol], and triglycerides].Body composition and anthropometric measurements (body fat percentage, body fat mass, weight, BMI [body mass index], and waist circumference).Quality of life (Diabetes 39, validated in the Mexican population).Lifestyle (IMEVID, validated for diabetes population in Mexico).Level of physical activity [IPAQ (International Physical Activity Questionnaire)].

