### Design and setting

A randomized controlled trial with three parallel groups, will be conducted across seven family medicine clinics of the Mexican Social Security Institute in Mexico City. The duration of intervention and follow-up is 12 months, with evaluations at baseline, 3, 6, 9 and 12 months. This study complies with international ethical standards and was approved by the National Research and Ethics Commission of the Mexican Social Security Institute, under the registration number R-2018-785-100. The clinical trial considers the effect of the mobile app + website vs. the website alone and a control group. It assumes a minimum clinically important difference (MCID) of 0.5% in HbA1c at 12 months. Based on the findings reported by Duke et al. (Cochrane 2009; ref. 23), who reported modest mean reductions in HbA1c with individual education (−0.3% in participants with a baseline HbA1c > 8%), a reduction of 0.5% was considered; a standard deviation (SD) of 1.3% was assumed based on reports from primary care cohorts and registry data, where the SD of HbA1c typically ranges from 1.1% to 1.3%. Using the formula to compare two means with *α* = 0.05 (two-tailed) and 80% power: *n* per group = 2 × (Z1 − *α*/2 + Z1 − *β*)2 × *σ*2/*Δ*2 With Z1 − 0.025 = 1.96, Z0.80 = 0.84, *σ* = 1.3, and *Δ* = 0.5, the required sample size was 106 participants per group. Taking into account a 20% loss, this resulted in 133 per group, and for greater conservatism, 136 participants per group were recruited (22).

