**Figure 5 F5:**
[figure not shown]
Follow-up and procedures.

**Primary measurements**: A1c (Basal and 12 months).

**Secondary measurements**: Lipid profile. Anthropometry and body composition. Lifestyle. Quality of Life. Physical Activity Level. (Basal and 12 months). Medical and Nutritional Therapy. In the baseline phase, participants will receive a complete plan that will include dietary and physical exercise recommendations, together with the collection of sociodemographic, clinical and biochemical data. Blood pressure will be taken, and relevant questionnaires will be administered. At 12 months, biochemical and anthropometric data will be reevaluated, and appropriate instruments will be applied. Follow-up visits will be scheduled at 3 and 6 months to reinforce medical and nutritional interventions.

At baseline, a comprehensive assessment will be conducted, including dietary and physical activity recommendations, collection of sociodemographic, clinical and biochemical data, blood pressure measurements and administration of standardized questionnaires. These evaluations will be repeated at 6 and 12 months. Additional follow-up visits at months 3 and 6 will reinforce interventions. Visit time points and assessments are summarized in Table 1.

**Table 1 T1:** Schedule of assessments.

Measurements during the intervention		Months			
	Basal	3	6	9	12
Medical examination to obtain sociodemographic and clinical data, measurement of systolic and diastolic blood pressure	X				
Biochemical data in blood samples (A1c, glucose, serum creatinine, total cholesterol, triglycerides, LDL-c and HDL-c).	X				X
Measurements of body weight, height, waist circumference, fat percentage, fat mass and lean mass	X	X		X	X
Medical and nutritional therapy, 24 h food reminder record.	X	X		X	X
Lifestyle (IMEVID), Quality of Life (Diabetes 39) Physical Activity Level (IPAQ)	X		X		X
Creation of users to the educational website and/or mobile App	X^a^				
Telephone call to reinforce the intervention group			X		

a For groups with educational website and mobile app + educational website.

The inclusion and follow-up of participants in the study is shown in Figure 6. The study follows the Standard Protocol Elements for Randomized Clinical Trials guidelines.

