### Results of the study

Primary objective. To evaluate the effect on metabolic control through the measurement of A1c levels and fasting glucose before and after 12 months of intervention. The measurement will be considered a continuous variable to identify achievement in metabolic control from A1c (≤7%). Secondary objectives. To assess changes in lipid profile (total cholesterol, LDL-c, HDL-c, and triglycerides), and body composition (weight, BMI, fat percentage, fat mass, and waist circumference. After the intervention, it will be possible to compare the clinically significant results of the metabolic variables in control targets: HbA1c % (≤7%), fasting glucose mg/dl (≤130), cholesterol mg/dl (≤200), LDL-cholesterol mg/dl (≤100), HDL-cholesterol mg/dl (≥40 men and ≥50 women) and triglycerides mg/dl (≤150).

The assessment of lifestyle through IMEVID, validated in the population with diabetes in Mexico, will be treated as a categorical variable, ranging from adequate and regular to inadequate lifestyle. Quality of life will be assessed through Diabetes-39, which includes different components of quality of life and will be analyzed as a categorical variable.

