### Statistical analysis

Descriptive statistics will be used with measures of central tendency and dispersion for quantitative variables that have a parametric distribution; variables with free distribution will be reported in median and interquartile range and will be presented in summary measurement tables. One-way ANOVA or Kruskal Wallis test will be used to compare the effect on clinical, anthropometric, and biochemical variables between groups. An X^2^ test will be used to evaluate the effect of the intervention between groups for metabolic control goals. An intention-to-treat analysis will be performed for the three groups in the clinical trial. In addition, a per-protocol analysis will be performed on the outcome variables according to compliance with the interventions. To this end, the level of compliance with the educational modules will be measured, as well as the use of the mobile application. A repeated measures ANOVA test will also be performed to analyze the effect of the intervention in each of the groups. A logistic regression model will be used to identify the effect of the intervention on the primary target variable, A1c, as a dichotomous variable in glycemic control and uncontrol. It will be adjusted for other variables, such as intervention group, years of diagnosis, physical exercise, schooling, marital status, and occupation.

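### The primary outcome is A1c and the trial is sized on its mean, but two sections blur this by adding fasting glucose and by attaching the primary label to dichotomised A1c

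*Protocol article*

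**What the plan says.** Four places in the protocol article agree on the variable:

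- Abstract, Methods: measurements "include A1c (primary outcome), lipid profile, anthropometry" and others.
- Objectives: "The primary objective of this clinical trial is to assess changes in A1c when comparing web-only, web + app, and usual care".
- Design and setting: "It assumes a minimum clinically important difference (MCID) of 0.5% in HbA1c at 12 months", followed by a two-means formula with SD 1.3, two-sided α 0.05 and 80% power, giving 106 per group.
- Follow-up and procedures, primary measurements: "A1c (Basal and 12 months". Neither fasting glucose nor a threshold is listed.

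Two places depart from this:

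- Results of the study puts two variables under its main aim, worded as "To evaluate the effect on metabolic control through the measurement of A1c levels and fasting glucose before and after 12 months of intervention". It goes on to give a continuous form and a 7% threshold in one sentence: "The measurement will be considered a continuous variable to identify achievement in metabolic control from A1c (≤7".
- Statistical analysis: a logistic regression for the effect "on the primary target variable, A1c, as a dichotomous variable in glycemic control and uncontrol", with covariate adjustment.

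For continuous A1c, the analysis section offers only the general sentence "One-way ANOVA or Kruskal Wallis test will be used to compare the effect on clinical, anthropometric, and biochemical variables between groups", plus a repeated-measures ANOVA. Neither is called primary.

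**The concern.** The protocol gives three candidate readings of its main result: a difference in mean A1c, a joint result on A1c and fasting glucose, and a difference in the proportion reaching A1c ≤7%. These can disagree. A treatment can shift the mean without moving many people across 7%, and glucose can move differently from A1c. In the analysis section, the word primary appears only in the sentence on the dichotomised form.

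Two things are at stake. The sample size supports only the first reading. And if the choice stays open until the data are seen, the reported result can follow whichever version is significant, which raises the false-positive rate above 5%.

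**Working it through.** **1. The plan's own figure.** Inputs from Design and setting: Δ = 0.5, σ = 1.3, z values 1.96 and 0.84.

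n = 2 × (1.96 + 0.84)² × 1.3² / 0.5² = 2 × 7.84 × 1.69 / 0.25 = 105.997, so 106 per group. Then 106 / 0.8 = 132.5, so 133; recruitment is set at 136, and 3 × 136 = 408. The arithmetic is right. Power for the mean difference is 80.0% at 106 per arm and 88.7% at 136.

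**2. The same effect expressed as A1c ≤7%.** The article gives no 12-month control rate for the trial, so I assume normal A1c with SD 1.3 in both arms and vary the usual-care mean μ:

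- p₁ = Φ((7 − μ)/1.3) under usual care
- p₂ = Φ((7 − μ + 0.5)/1.3) under intervention
- power = Φ((|p₂ − p₁| − 1.96·SE₀)/SE₁), with SE₀ from the pooled proportion and SE₁ from the separate proportions; two-sided 0.05, unadjusted

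Example at μ = 8.0 with 106 per arm: p₁ = 0.221, p₂ = 0.350, difference 0.129, SE₀ = 0.0620, SE₁ = 0.0614. This gives Φ((0.1294 − 0.1216)/0.0614) = Φ(0.127) = 55%.

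| Usual-care mean (assumed) | Controlled, usual care vs intervention | Power at 106 | Power at 136 (no loss) | n per arm for 80% |
|---|---|---|---|---|
| 7.25 | 42% vs 58% | 60% | 71% | 168 |
| 7.5 | 35% vs 50% | 60% | 71% | 170 |
| 8.0 | 22% vs 35% | 55% | 66% | 191 |
| 8.5 | 12% vs 22% | 46% | 56% | 240 |
| 9.0 | 6% vs 12% | 34% | 42% | 341 |

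A search over usual-care means puts the maximum at 7.25. The Background's national figure of 68% poorly controlled, taken as 32% controlled under usual care, gives 32% vs 47% and 59% power at 106 per arm.

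**3. Sensitivity to the SD.** With SD 1.1, the lower end of the range the article mentions, the ≤7% version reaches at most 75% at 106 per arm, against 91% for the mean. It passes 80% only with SD 1.1, no loss at all and a usual-care mean near 7.0 to 7.5 (about 84%). Those are not the plan's inputs.

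**4. Type I error if the version is chosen after seeing results.** I simulated the null with 20,000 trials per setting, 108 per arm, and tested mean A1c, mean glucose and the ≤7% proportion each at 0.05. The A1c–glucose correlation is not in the article, so I assumed 0.5 to 0.85, with A1c means of 7.5 to 9.0. The chance of at least one p < 0.05 is about 10–13%. This holds for three-arm omnibus tests (ANOVA and chi-square) and for a single pairwise contrast.

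**The case against.** The strongest reply is that the primary outcome is not really in doubt. Four places name A1c; the sample-size paragraph and the primary-measurements list give 12 months; the objectives and the sample size imply a continuous scale. The logistic-regression sentence can be read as saying that A1c is the primary variable and that this one model happens to use it dichotomised. The control targets, including HbA1c ≤7%, come after the secondary-objectives label and sit beside the lipid targets, which suggests a supportive role. A secondary responder analysis with less power than the mean comparison is ordinary. Choosing among several tests is often left to an analysis plan, and that plan is not shown.

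Most of this stands. A reader might infer that the trial has no fixed primary outcome, or that it is underpowered. The article supports neither: variable and time point are largely settled, and the power loss arises only if the dichotomised form is taken as primary, which the text does not clearly say.

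A reader might also reach a type I error near 26% by testing all three versions over three pairwise contrasts. That is not a fair charge here. About 12% already arises from three contrasts on mean A1c alone, a separate multiplicity question, and the between-group tests named are omnibus ones.

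The reply does not remove the contradictions. Fasting glucose is inside the primary objective in one section and absent from the primary measurements in another. One sentence joins a continuous variable to a threshold. These are conflicts in the stated text, and an unseen analysis plan does not make the sections agree.

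**Conclusion.** The point holds in a limited form. A1c at 12 months is the primary outcome on the balance of the document, and the sample size is correct for a difference in means. Left unsettled are whether fasting glucose shares primary status, whether the main result is a mean or a control rate, and which comparison delivers it.

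The 80% power does not carry over to the ≤7% form: with the plan's shift and SD it is at most about 60% at 106 evaluable per arm, falling to 34% at a usual-care mean of 9.0%. This rests on normality, an assumed usual-care mean and an unadjusted test; the effect of covariate adjustment was not modelled. The 10–13% type I error rests on assumed correlations and on selective reporting actually taking place. It is a risk the wording leaves open, not something the plan sets out to do.

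This should be fixed, but it does not undermine the design.

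**What to change.** In Results of the study, state continuous A1c at 12 months as the sole primary endpoint, in line with the objectives, the sample size and the primary-measurements list. Move fasting glucose and the proportion with A1c ≤7% to the secondary outcomes, and remove the threshold from the sentence that calls the measurement continuous.

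In Statistical analysis, name one between-arm comparison of mean A1c as the primary analysis. Describe the logistic regression as a secondary analysis of glycaemic control, without the primary label.

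The cost is a few sentences in two sections, with no new data, visits or participants and no change to the sample size. It should be done before outcome data are seen by arm, because a choice made afterwards cannot be shown to be independent of the results.

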## Discussion

This study evaluates the impact of the “I Understand My Diabetes” platform, a digital educational tool combining professional care with a self-paced learning model, on metabolic control among individuals with T2D.

Previous research by our team demonstrated a significant HbA1c reduction (–0.73%) after a 21-month website-based intervention in Mexico (18). Unlike the prior study, this intervention allows patients to access content asynchronously, enhancing accessibility and scalability.

Educational website content was validated by clinical experts and usability-tested in the target population.

Some of the limitations commonly reported in mHealth studies include the lack of content validation by healthcare professionals, as well as low acceptance and perceived usefulness by end users (13). Thus, the study performed content validation of the educational website through expert consensus (28) and measured the usability of the web content among end users (17).

It has been reported that technology-based interventions implemented in patient care clinics, with reinforcement by health professionals, improve knowledge about the disease and promote healthier lifestyles (20, 21).

Systematic reviews have documented the use of mobile apps for various purposes, ranging from collecting self-care data to evaluating healthcare professionals or patients (14). However, adherence to mHealth-supported strategies for monitoring, diet, physical exercise, and professional reinforcement tends to be higher in the short term but decreases over time (29). Therefore, improving usability may enhance adherence to mHealth interventions. The use of mHealth has been shown to improve lifestyle and reduce HbA1c in the short term, with smaller effects observed in the long term (12).

This study aims to evaluate the impact of delivering diabetes education via a website and mobile app that provide diet and physical exercise plans, while also linking with the health professionals' records, to provide more comprehensive information to the users.

The objectives of mobile app interventions vary widely, ranging from insulin dose control to improving diabetes knowledge and glucose monitoring through strategies such as text messages, health diaries, and virtual counseling (15). Although mHealth has been shown to complement diabetes care, particularly in developed countries, these tools should be regulated, designed by diabetes clinical experts, validated with clear objectives, tailored to users' needs, rendered easy to use, and focused on desired outcomes (30).

In Mexico, Internet and technology use in healthcare is increasing, both for care management and use by participants at home. However, socioeconomic, cultural, political, and economic barriers remain, alongside limited investment, low digital literacy among health professionals, and challenges implementing technology for diabetes care and prevention. It is necessary to design strategies that integrate digital tools into diabetes care, facilitating communication with physicians and empowering patient self-management.

The Mexican health system is divided into public and private sectors; the Mexican Social Security Institute (IMSS), part of the public sector, serves the largest proportion of the population, approximately 51.0% of those entitled in 2020 (31). By 2023, IMSS is projected to provide nearly 3.5 million consultations in primary care clinics to people living with diabetes (32).

Therefore, there is a significant opportunity to consolidate health promotion and secondary prevention strategies mediated by digital health and led by health professionals. This study seeks to evaluate the effectiveness of providing asynchronous diabetes education through a website with monitoring and promotion of a healthy lifestyle, using mHealth as a tool to improve metabolic control and healthcare outcomes.

### Data management

The data generated in the study will be stored in both physical repositories and digital media, with the responsible personnel verifying the capture date and time of each record. Data entry will utilize computer systems that ensure verification and readability. Information will be stored on digital media structured through an information architecture designed specifically for the study's purposes.

Data recording, retrieval, updating, and deletion will be performed securely, maintaining a historical record. Access to the registry and data retrieval will be controlled through access levels, permissions, and digital credential verification. System access will require user authentication.

### Data privacy and security

Before registering study participants in the mobile application, which handles sensitive data, a privacy notice will be displayed specifying the data that will be collected, how it will be used during the study, and the security measures in place to protect this information.

The notice will describe the sociodemographic, laboratory, clinical, and contact data required, clarifying that it will only be used by the Mexican Social Security Institute. Participants will also be informed of their rights regarding their data and provided contact information for any questions related to data use and security.
